## Abstract

**Background:**

Innovative approaches are needed to maximise the uptake and sustainment of evidence-based practices in a variety of health service contexts. This protocol describes a study that will seek to characterise the potential of one such approach, user-centred design (UCD), which is an emerging field that seeks to ground the design of an innovation in information about the people who will ultimately use that innovation. The use of UCD to enhance strategies for implementation of health services, although promising, requires a multidisciplinary perspective based on a firm understanding of how experts from each discipline perceives the interrelatedness and suitability of these strategies.

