## Methods

### Participants

We will recruit implementation science experts (*n* = 30) and UCD experts (*n* = 30) to participate in this study. Expertise will be self-reported and can be based on experience in research, practice/industry, and/or education over the past 5 or more years. Our planned enrolment is twice the recommended sample size for concept mapping (*n* ≥ 15 per participant group; see [33]) to ensure that we can make meaningful comparisons between results from implementation versus UCD experts.

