### Idea generation

The first step of concept mapping involves the generation of the ideas or concepts that participants will sort and rate [32]. We completed idea generation as a research team by using existing resources that documented implementation and UCD strategies to generate a comprehensive list of 66 strategies (36 implementation, 30 UCD). The third and fourth authors served as expert consultants regarding UCD and implementation strategies, respectively, but all team members reviewed the full list of strategies. Each strategy has a short name as well as a more comprehensive, yet still brief (< 50 words), definition. Tables 1 and 2 present the full list of strategies; a list of the definitions is available from the first author upon request. After finalisation of the lists of strategies, we uploaded each strategy into CSGM as a separate ‘statement’ for subsequent sorting and rating by participants.

**Table 1 Tab1:** List and characteristics of implementation strategies generated for sorting and rating

Implementation strategy	ERIC results^a^		Primary CFIR domain(s)^b^			
	Importance	Cluster	OS	IS	ID	IN
Access new funding	3.57	F	X			
Alter incentive/allowance structures	3.17	F	X	X		
Alter patient/consumer fees	2.60	F	X	X		
Assess for readiness and identify barriers and facilitators	4.60	E	X	X	X	
Audit and provide feedback	4.40	E			X	
Build a coalition	3.77	S	X	X		
Centralise technical assistance	2.73	I	X			
Change accreditation or membership requirements	2.17	CI	X			
Change record systems	2.83	CI		X		
Conduct local consensus discussions	3.63	S		X		
Conduct ongoing training	4.17	T			X	
Create or change credentialing and/or licensure standards	2.23	CI	X			
Develop and implement tools for quality monitoring	4.37	E				X
Develop and organise quality monitoring systems	4.33	E		X		
Develop educational materials	3.80	T				X
Develop resource sharing agreements	3.07	CL	X			
Facilitate relay of clinical data to providers	4.17	CL		X		
Facilitation	4.13	I		X	X	
Fund and contract for the clinical innovation	3.67	F	X			
Identify and prepare champions	4.20	S			X	
Increase demand	3.30	CO	X			
Involve patients/consumers and family members	3.87	CO			X	
Mandate change	3.23	CI	X	X		
Obtain formal commitments	3.77	S	X			
Organise clinician implementation team meetings	3.97	S		X		
Place innovation on fee for service lists/formularies	3.40	F	X			
Promote adaptability	3.90	A				X
Provide local technical assistance	3.97	I		X		
Provide ongoing consultation	4.17	T			X	

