### Participant questions

Participants will report on key demographic variables in CSGM. Importantly, each participant will self-identify their primary professional expertise as ‘implementation expert’ or ‘UCD expert’; we expect that some participants will have expertise in both areas but we will ask each to choose a primary area. Responses to this question will subsequently be used to compare the responses of implementation versus UCD experts. Four other questions will collect descriptive information and also serve as prompts to help participants reflect on professional experiences that are relevant to the sorting and rating tasks. Specifically, participants will report how many years of experience they have in their area of expertise; the percentage of their time spent on implementation and/or UCD activities that involved interdisciplinary collaboration; which primary service sectors (e.g. healthcare, education, human services, prevention and health promotion) are the focus of their work; and which system level they primarily seek to influence through their work (i.e. the CFIR [9] intervention, individual, inner setting, and outer setting domains). CSGM only allows for five participant questions, so additional demographic data will be collected in the post-survey instead.

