### Sorting and rating

The middle two phases of concept mapping, namely sorting and rating [32], occur in tandem and will involve collecting input from a sample of individuals with content expertise through the CSGM platform. For the sorting step, participants will sort virtual cards that represent the 66 implementation and UCD strategies into groups. Each card will present the name of a strategy, followed by its definition; longer definitions will not be fully displayed in standard view, but the participant can click a button on the card that will expand it and display the full definition. The order of card presentation will be randomised, with no distinction made between implementation versus UCD strategies. Participants will be instructed to group the strategies according to their view of their meaning or theme and to give each group a name that describes its theme or contents; approximately 5 to 20 groups are expected given the number of strategies to be sorted. Participants will be instructed to not create groups according to priority (e.g. ‘First Steps’) or value (e.g. ‘Important’), to avoid catch-all groups (e.g. ‘Miscellaneous’), and to sort all of the cards even if that means creating groups that only contain one card.

For the rating step, participants will rate each strategy on its importance and feasibility on a scale ranging from 1 (least important/feasible) to 5 (most important/feasible). The strategies and their definitions will be presented in list format during this step, with the rating scale next to each strategy, and the list will be prefaced by the following instructions: “Please select a number from 1 to 5 for each discrete strategy to provide a rating in terms of how important (feasible) you think it is for the improvement of health and social services. Keep in mind that we are looking for relative importance (feasibility), and use all the values in the rating scale to make distinctions.” Our rating dimensions and instructions were adapted from the ERIC study [8].

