After we have selected the final set of clusters, we will characterise the importance and feasibility ratings for each cluster and strategy. We will use CGSM to visually represent the relationships among concepts using go-zone graphs that plot clusters and strategies along key dimensions (e.g. plots of importance vs. feasibility). Go-zone graphs using construct means as graph axes can be used to characterise ‘Go/No-Go/Proceed-With-Caution’ zones among the four quadrants of a scatterplot; these zones will illustrate which clusters are particularly promising for future actions such as collaboration among implementation experts and UCD experts. Moreover, to promote deeper understanding of the connections between implementation and UCD, we will also explore the level of convergence (i.e. extent to which concepts represent overlap between fields) and divergence (i.e. extent to which concepts represent unique contributions from a single field) in our findings by inspecting the number and types of strategies in each cluster.

Following the aforementioned initial analyses of concept mapping data, which will examine results across rating and sorting data from all participants, we will also examine results separately for each subgroup of experts (i.e. implementation vs. UCD). Specifically, we will apply the same analytic approach described previously with data separated by professional expertise, and we will examine differences in (1) the number and contents of clusters and (2) the ratings of each cluster. Within CSGM, we will generate the same data visualisations (e.g. concept maps, ladder graphs, go-zone graphs) separately for each group. Outside of CGSM, we will use multivariate general linear models to examine between-group differences in average ratings of importance and feasibility across professional expertise and clusters, and we will also use χ^2^ analyses to examine differences between professions in the amount of convergence and divergence in clusters.

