More specifically, the results of the present study will inform our perspectives on the potential for integrating UCD into implementation science in several ways. First, the clusters of strategies generated will deepen our understanding of how UCD strategies relate to traditional implementation strategies. For example, it may be ideal for implementation and UCD experts to work side-by-side to execute strategies from more convergent strategy clusters (i.e. several implementation and UCD strategies that focus on the same or related goals), whereas experts might better work sequentially or in parallel for more divergent clusters (i.e. groups of implementation or UCD strategies that have little direct overlap with strategies from the other discipline). Second, data on the importance and feasibility of clusters and strategies will be used to characterise their promise for interdisciplinary integration. For instance, we will prioritise clusters and strategies in the ‘Go’ zone (high importance and feasibility) of the Go-zone graph in future work seeking to promote collaboration, whereas strategies and clusters in the ‘No-Go’ zone (low importance and feasibility) will be de-emphasised. Third, to the extent that perspectives differ between implementation experts and UCD experts, we will use that information to identify areas of particular challenge in bridging perspectives across these two disciplines. Additional research may be necessary to resolve discrepancies; for example, if experts in one discipline view the strategies as more divergent or less important than do experts in the other, it will be important to understand the reasons for those discrepancies and refine our conceptualisation of the strategies accordingly. Finally, the post-survey questions about supporting collaboration will help identify potentially useful approaches for joining implementation experts and UCD experts together so that they can put into practice the interdisciplinary perspectives identified in this study. Specific approaches to collaboration will also likely merit additional investigation as we move this line of research forward.

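### The formal test of profession differences in ratings uses cluster averages with no term for a strategy's field of origin, so opposite own-field preferences shrink in mixed clusters and cancel near an even mix

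*Protocol article*

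**What the plan says.** Participants rate "a comprehensive list of 66 strategies (36 implementation, 30 UCD") for importance and feasibility on a scale from 1 to 5 (Idea generation; Sorting and rating). Each participant names one primary field of expertise, and "Responses to this question will subsequently be used to compare the responses of implementation versus UCD experts" (Participant questions).

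The Analytic strategy section then sets the between-profession comparison of ratings at the level of the cluster. The formal analysis is a multivariate general linear model "to examine between-group differences in average ratings of importance and feasibility across professional expertise and clusters". Profession and cluster are the factors named; a strategy's field of origin is not.

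The same section also plans descriptive work at strategy level. Ratings are summarised for strategies as well as clusters, go-zone graphs plot both, and these graphs are repeated separately for each profession. Professions are further compared on the number and contents of clusters and, by chi-square, on convergence and divergence.

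The Discussion gives mixed clusters a particular use: "it may be ideal for implementation and UCD experts to work side-by-side to execute strategies from more convergent strategy clusters". It also says that differences between the two groups of experts will be used to find where the disciplines will be hard to bring together.

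**The concern.** Experts from two fields rate strategies from both. A plausible pattern is that each group rates its own field's strategies higher than the other group does, through preference or greater familiarity. In a cluster drawn from one field, that pattern moves the cluster average fully in one direction. In a cluster drawn from both fields, it moves some items up and others down, and averaging offsets the two.

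The stated comparison is therefore least sensitive in the mixed clusters, which are the ones the study calls convergent. Fitting a profession-by-cluster interaction would not restore what is lost, because the offset happens inside each cluster average before any model is fitted. At stake is the Discussion's use of profession differences to locate difficulty: for the same strength of preference, single-field clusters would be flagged and mixed clusters could pass unnoticed.

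**Working it through.** **Inputs from the protocol article.** The stated counts reproduce: 36 + 30 = 66 strategies, and 2 × 15 = 30 participants per profession (Participants: "Our planned enrolment is twice the recommended sample size for concept mapping", the recommendation being at least 15 per group). No alpha, power, standard deviation or expected preference is given.

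**Assumed inputs.** Own-field preference b = 0.3, 0.5 or 1.0 points; two-sided alpha 0.05; SD of a rater's cluster mean 0.5 or 0.7.

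**Formula.** Let p be the UCD share of a cluster and take differences as UCD experts minus implementation experts. The difference is +b on UCD strategies and −b on implementation strategies. The difference in the cluster average is

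b·p − b·(1 − p) = b(2p − 1).

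| UCD share p | b = 0.3 | b = 0.5 | b = 1.0 |
|---|---|---|---|
| 1 (all UCD) | +0.30 | +0.50 | +1.00 |
| 0.75 | +0.15 | +0.25 | +0.50 |
| 0.6 | +0.06 | +0.10 | +0.20 |
| 0.5 | 0 | 0 | 0 |
| 0 (all implementation) | −0.30 | −0.50 | −1.00 |

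Over the whole list, p = 30/66 = 0.455, and with b = 0.5 the difference is 0.5 × (0.909 − 1) = −0.045.

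**Unequal preference.** If the gap is b_U on UCD strategies and b_I on implementation strategies, the difference is p·b_U − (1 − p)·b_I. With b_U = 0.5 and b_I = 0.3, an even cluster shows 0.25 − 0.15 = 0.10, and the zero point moves to p = 0.3/(0.5 + 0.3) = 0.375. Asymmetry moves the point of cancellation; it does not remove it.

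**Power of the cluster-average comparison** (30 per group, b = 0.5, one cluster at a time):

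| Share from the larger field | Difference (size) | SD 0.5 | SD 0.7 |
|---|---|---|---|
| 0.5 | 0 | 5% | 5% |
| 0.6 | 0.10 | 12% | 8% |
| 0.75 | 0.25 | 49% | 28% |
| 1 | 0.50 | 97% | 79% |

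The 5% in the first row is only the false-positive rate.

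**Check by simulation** (4000 runs, 30 per group, 8-item cluster, assumed rater SD 0.4 and item SD 0.9). The implied SD of a rater's cluster mean is √(0.16 + 0.81/8) = 0.51, in line with the first SD above. Each cell gives the power of the cluster average, then of a profession-by-field contrast on the same ratings.

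| Items from each field | b = 0.3 | b = 0.5 |
|---|---|---|
| 4 + 4 | 5% vs 94% | 5% vs 100% |
| 5 + 3 | 9% vs 94% | 16% vs 100% |
| 6 + 2 | 21% vs 88% | 48% vs 100% |

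In these runs the ratings already collected hold the information. The cluster average discards it.

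**The case against.** **Strategy-level results are planned.** Go-zone graphs plot strategies and are drawn for each profession. Placed side by side, they could show the two fields' items shifting in opposite directions. This stands, and it means that professions are not compared by cluster average alone. It does not fill the gap in the formal test, since no stated contrast or rule reads those graphs for this purpose.

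**Everything about the preference is assumed.** Its existence, symmetry and size are not in the documents, and complete cancellation needs a roughly even cluster. This stands too: in uneven clusters the effect is attenuated, not removed.

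**A condensed article may leave model terms to a fuller plan.** This is partly fair, and a fuller plan may contain the term. But the article itself names the unit of analysis and the two factors, and the point concerns that stated choice.

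A reader might also infer three stronger things that the documents do not support:

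- *That a small profession difference would count as joint endorsement of a mixed cluster.* The Discussion ties side-by-side work to the composition of the cluster, and priority to its go-zone position. Nothing treats a null rating difference as endorsement.
- *That differences in single-field clusters would be artefacts.* If UCD experts rate UCD strategies higher than implementation experts do, that is real disagreement, and describing it is an aim of the study.
- *That the ratings were meant to be masked to field and the masking fails.* The statement "The order of card presentation will be randomised, with no distinction made between implementation versus UCD strategies" describes the cards in the sorting task. No masking is claimed for rating, and the cancellation does not depend on raters recognising a strategy's origin.

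**Conclusion.** The point holds as a limitation of the one formal comparison of ratings between professions. That comparison uses cluster averages without strategy field, so opposite own-field preferences are attenuated by the factor (2p − 1): to half at a 75/25 mix and to zero at an even mix. With b = 0.5 and 30 per group, the power to see the difference in a 75/25 cluster is about 28% to 49%, against 79% to 97% in a single-field cluster, for SDs of 0.7 and 0.5. The test can miss disagreement in convergent clusters; it will not necessarily do so.

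The formula is exact for the symmetric preference described. The sizes rest on assumed values of b and SD. The consequence is confined to the Discussion's use of profession differences to locate difficulty, which would lean towards single-field clusters. The clusters themselves and the overall go-zone results are not called into question. This is a worthwhile improvement at almost no cost, and not an error that invalidates the plan.

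**What to change.** Add strategy field (implementation or UCD) and its interaction with profession to the rating model. In practice, average each participant's importance and feasibility ratings separately over the 36 implementation and the 30 UCD strategies, and compare the two professions on both averages and on their difference. This estimates the own-field preference directly instead of assuming it.

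Then, for each mixed cluster, report the profession difference separately for its implementation and its UCD strategies, with confidence intervals, since some parts may rest on one or two strategies. Single-field clusters have only one part and need no change.

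Profession, item ratings and each strategy's field (Tables 1 and 2) are already available, so the cost is a small amount of analysis and reporting. No change to recruitment, tasks or sample size is needed.

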### Analytic strategy

After sorting and rating are complete, the final step of concept mapping is data analysis [32]. In addition to analyses of concept mapping data, we will use software programmes such as Excel and SPSS to examine descriptive statistics (e.g. means, standard deviations, frequency counts) for demographic variables and survey responses (e.g. ratings of collaboration options). As noted previously, we will analyse data provided by all participants (including those who do not complete all study steps), which could result in uneven numbers of implementation experts versus UCD experts for certain analyses. This is not a problem in concept mapping because the technique does not rely on traditional assumptions for statistical significance and power [33].

The analytic strategy for concept mapping data requires further explanation. To start that process, we will use multidimensional scaling techniques (embedded in CSGM [37]) to identify clusters of implementation and UCD strategies that were generated most consistently across participants. CSGM will empirically generate any number of clusters that the researcher specifies, but it is up to the researcher to select the appropriate set of clusters (e.g. there is no established cut-off for minimum bridge values, which represent the closeness of relationships between concepts in a cluster, that indicate ‘good’ clusters). Consistent with the ERIC study [8], the research team will review the results for conceptual clarity and credibility before selecting which set of clusters to report in our findings. To guide that process, we will examine visual summaries of the data that can be produced in CGSM, such as cluster maps, which represent the relatedness of concepts within and between clusters in terms of visual distance and can be weighted by key dimensions (e.g. importance, feasibility), and ladder graphs, which provide a visual representation of the relationship between dimensions (e.g. importance and feasibility) within and across clusters. We will also consider the extent to which clusters are consistent with or expand upon the (1) clusters of implementation strategies identified in the ERIC study [8], (2) CFIR domains [9], and (3) the Promoting Action on Research Implementation in Health Services framework [41], which describes implementation of research evidence in practice contexts.

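### The chi-square test of convergence between professions names no unit, and its two natural units, strategies and clusters, are not independent observations

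*Protocol article*

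**What the plan says.** All of this is in the protocol article, under Analytic strategy unless stated.

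- Multidimensional scaling in the mapping software is used "to identify clusters of implementation and UCD strategies that were generated most consistently across participants". A map is thus a product of pooled sorts, not of one person's sort.
- Convergence and divergence are explored "by inspecting the number and types of strategies in each cluster".
- For the professions, "we will apply the same analytic approach described previously with data separated by professional expertise". This gives one map for implementation experts and one for UCD experts.
- The number of clusters is open: "CSGM will empirically generate any number of clusters that the researcher specifies", and "it is up to the researcher to select the appropriate set of clusters" after reviewing the results for clarity and credibility.
- Outside the mapping software, chi-square is used for "analyses to examine differences between professions in the amount of convergence and divergence in clusters". No unit, table layout, cut-off for a convergent cluster, significance level, pairing or resampling is given.
- Both professions sort the same 66 strategies, 36 implementation and 30 UCD (Idea generation).
- Planned enrolment is 30 experts per profession, twice the recommended minimum of 15, so that the professions can be compared meaningfully (Participants).

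**The concern.** A chi-square test needs counts of independent observations. The independent units here are the experts, but convergence as described is a property of a cluster in a map made from all experts of a profession. Two tables follow naturally from that description.

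- **Strategies.** The table is 66 v 66. The same items are classified twice, and every strategy in a cluster takes that cluster's label, so labels change in blocks.
- **Clusters.** The table holds a handful of clusters per map. The team chooses how many after seeing the results, and both maps are built from the same items.

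In neither table is an expert an observation. The total is 132 strategies, or the chosen number of clusters, whether 15 or 30 experts sort. The enlarged sample can make the maps more stable, but the test's reference distribution takes no account of it.

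The Discussion says that if one discipline sees the strategies as more divergent, the team will seek the reasons and refine its conceptualisation. A spurious difference could misdirect that work, and an over-conservative test could miss a real one.

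**Working it through.** The article gives no figure for this test, so there is none to reproduce. The check has three parts.

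**1. One pair of maps, two units.**

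Inputs from the article: 66 strategies and two maps. Assumption: 9 clusters per map, so 66/9 ≈ 7.3 strategies each. Suppose the maps differ by two clusters changing label, which moves about 14 strategies.

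For a 2×2 table, χ² = N(ad − bc)² / (product of the four margins).

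- Strategies, 33 v 47 of 66 in convergent clusters: 132 × (33×19 − 47×33)² / (66×66×80×52) = 132 × 924² / 18,120,960 = 6.22, p = 0.013. With Yates' correction: 132 × (924 − 66)² / 18,120,960 = 5.36, p = 0.021.
- Clusters, 4 v 6 of 9 convergent: 18 × (4×3 − 6×5)² / (9×9×10×8) = 18 × 324 / 6,480 = 0.90, p = 0.34. With Yates' correction, p = 0.64.

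A difference of about two clusters is significant under one count and far from it under the other.

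**2. Expected counts with clusters as the unit.**

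With k clusters in each map and m convergent clusters in total, the smallest expected count is min(m, 2k − m)/2, which is at most k/2. For k = 9 it cannot exceed 4.5, so it is always below 5.

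**3. Rejection rates when the professions do not differ.**

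Both simulations drew 30 v 30 experts from one sorting distribution, with 66 strategies and 5–20 piles per expert (the range expected under Sorting and rating). They then used two-dimensional scaling and Ward clustering. The following are assumptions, not in the article: a 5% level, Ward clustering, the sorting model, the number of clusters and the definition of convergence.

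- Simulation A: 10 or 8–12 clusters; convergent if the minority field is at least 20–25%; 16 scenarios × 250 runs.
- Simulation B: 5, 9 or a free 5–12 clusters; convergent if there is any mixing or if the minority field exceeds 25%; four-dimensional latent structure, field separation 1–2, noise 0.7–1.5; 24 combinations × 400 runs.

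| Unit counted | A | B, uncorrected | B, Yates |
|---|---|---|---|
| Strategies | 20–33% | 19–58% | 15–54% |
| Clusters | 0–1.2% | 0–3.3% | 0–0.7% |

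In B the smallest expected count in the cluster table was below 5 in 96–100% of runs. As a reference, truly independent clusters, 9 v 9, gave 4.9–5.6% uncorrected. Small counts alone therefore do not explain the low cluster-level rates, which points to dependence between the maps.

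**The alternative, under the same kind of model.** Profession labels were permuted over the 60 experts and both maps rebuilt (9 clusters, 99 permutations, 120 runs). This rejected in 2.5% and 6.7% of null runs under the two definitions of convergence. The simulation standard error at 5% is √(0.05×0.95/120) = 2.0 percentage points, so both agree with 5%. In the same runs the strategy chi-square rejected in 39% and 40%, and the cluster chi-square in 0% and 0.8%. Under one large true difference (60 runs) the rates were 98% for permutation, 100% for the strategy chi-square and 85% for the cluster chi-square.

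**The case against.** **The unit is inferred.** The article does not say that strategies or clusters will be counted, and a condensed article may leave the table layout to a fuller plan. Individual sorts are collected, so an expert-level score would be possible and sound. A reader might infer that the test is invalid whatever the unit. The document does not support that; the criticism covers the two units that follow from how convergence is scored. Within that scope it stands, because the article describes no expert-level score or resampling.

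**The two counts fail differently.** Only the strategy count creates false differences. The cluster count is conservative. It would also be too strong to say that it can detect nothing, since it rejected in 85% of runs under a large true difference. With 10 v 10 clusters, a split of 8 v 3 reaches p = 0.025 uncorrected but 0.072 with Yates' correction, and the article does not say which would be used.

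**Concept mapping is said not to rely on traditional assumptions for significance and power.** That remark concerns uneven group sizes within the mapping technique. It does not cover a conventional significance test run outside it.

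**The comparison is a supplement.** A reader might take this test to decide a principal aim. The aims at the end of the Background do not list it, and the convergence named in the abstract is between the two fields, not between two groups of raters. The professions are also compared descriptively through separate maps and cluster contents. This stands and limits the severity.

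**Conclusion.** The concern holds for the two natural readings of the planned test. The chi-square is anti-conservative if strategies are counted (about 15–58% rejection at a nominal 5%) and conservative, with small expected counts, if clusters are counted (about 0–3%).

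The direction was the same in both simulations and in all 24 combinations of the second. The figures themselves rest on the assumed sorting structure, number of clusters and definition of convergence, and should be read as orders of magnitude.

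Severity is moderate. The comparison is exploratory, with no significance level or decision rule attached, and the descriptive comparison of maps is unaffected. It still merits correction, because the Discussion plans follow-up work on differences between the professions and a better-calibrated test can be run on data already being collected.

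**What to change.** 1. Define convergence before the profession maps are seen: what makes a cluster convergent, and the summary compared between maps, for example the share of the 66 strategies lying in convergent clusters.
2. Replace the chi-square with a permutation test. Reassign the profession label over the experts who sorted, keeping the actual group sizes, and rebuild both maps each time. Refer the observed difference to the resulting distribution.
3. Set the rule for the number of clusters in advance and apply it identically to every map, observed and permuted. It may be a fixed number, or an automatic rule that lets the number differ between professions. Maps chosen for conceptual clarity can still be reported, but a choice by judgement cannot be repeated inside the permutations.
4. If this is not done, report the map comparison descriptively and give no p-value.
5. As an optional complement, compute for each expert the share of co-sorted pairs that join an implementation strategy to a UCD strategy (36 × 30 = 1,080 possible cross-field pairs). Report the difference between professions with a 95% CI. This is a different estimand from cluster convergence and should be labelled so.

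The cost is a change of wording and a short script on the individual sorts, assuming that they can be exported from the mapping software. No new data are needed. The downside is a little more work outside that software, where the article already plans analyses.
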